#### Withdrawal criteria

2.3.3

1.After inclusion, it was found that they were not suitable to continue to participate in the study.2.Those who fail to treat according to the regulations affect the evaluation of curative effect.3.Withdrawal of consent by the subject or a legal representative.4.Loss to follow-up.5.Serious adverse events.6.Significant errors or deviations were found in the clinical protocol.7.New infarct or secondary hemorrhage occurred and the condition deteriorated.

### Study settings and recruitments

2.4

The present study will be conducted in the Shaanxi Province Hospital of Traditional Chinese Medicine.

This study intends to recruit patients diagnosed with acute ischemic stroke within 1 month in the outpatient and inpatient departments of Shaanxi Provincial Hospital of traditional Chinese medicine. At the same time, posters, leaflets, and publicity should be put up in a prominent position in the hospital, so that patients can have regular free examination, which will help to successfully complete the recruitment work. At the same time, the official website, wechat, and microblog of Shaanxi Provincial Hospital of traditional Chinese medicine are powerful publicity methods.

### Study group

2.5

In this study, 42 patients who met the inclusion criteria and obtained informed consent were selected as the research subjects. The subjects were randomly divided into 2 groups according to the ratio of 1:1: the experimental group and the control group, with 21 cases in each group.

### Study time

2.6

This clinical study will be conducted from August 1, 2019 to August 1, 2021.

### Interventions

2.7

The intervention measures involved in this study are based on the theory and professional practice knowledge of traditional Chinese medicine. The doctors who are in charge of operating the instruments for treatment have obtained the practicing certificate issued by the national health and Health Commission, and have received more than 3 years of clinical skills training in acupuncture and rTMS. Patients in the experimental group were treated with rMS in M1 area of healthy side, PC6, and SP6 on the affected side, while patients in the control group received acupuncture treatment. In addition, both groups were given basic treatment.

#### Experimental group

2.7.1

rTMS therapeutic instrument (ccy-ii, Wuhan yiruide medical products New Technology Co, Ltd, Wuhan) was used. According to the theory of modern neural rehabilitation,^[15,16]^ rTMS stimulation of contralateral M1 area was applied to the rehabilitation of limb function after stroke. According to the Xingnao Kaiqiao acupuncture method created by [name], academician of Chinese Academy of engineering and master of Chinese medicine,^[17,18]^ PC6 and SP6 on the affected side were selected as the operation sites. After rest preparation, the transcranial magnetic stimulation technology and resting motor threshold (RMT) were tested: the patients took standard sitting posture, maintained emotional stability, and muscle relaxation. When stimulating M1 area, the coil should be tangent to the scalp. Adjust the coil to obtain the maximum amplitude and the best MEP repeatability. The stimulation intensity will start from 30% and increase gradually at the rate of 2.5%. The minimum stimulus intensity (RMT) was 5 abdominal contractions of the contralateral abductor brevis muscle in 10 consecutive stimuli; localizing the stimulation area: when stimulating the motor cortex of the thumb on the right dorsolateral prefrontal cortex (r-dlpfc) on the scalp, the stimulation coil was placed on the right dorsolateral prefrontal cortex (r-dlpfc) on the scalp, then 6 cm to the right; during peripheral stimulation, the stimulation coil will be placed on the affected side of PC6 (located on the palmar side of the forearm, on the line between Quze acupoint and DalingQuze acupoint, 2 inches on the transverse line of the wrist, between the tendon of palmaris longus and the flexor carpi radialis) (Fig. 2). The stimulation coil will be placed at the SP6 on the affected side (3 inches above the tip of the medial malleolus, and the posterior edge of the tibia is close to the bone edge depression) (Fig. 3); setting stimulation parameters: according to the different stimulation sites, different standard stimulation intensity modes were selected: the frequency was 1 Hz, the total number of pulses was 900, and the intensity of RMT was 90%; in the peripheral PC6 and SP6 position, the frequency was 3 Hz, the total number of pulses was 450, and the intensity of RMT was 90%. After checking the above parameters, the stimulation was started and the loop valve was removed. Participants will be treated once a day for 25 minutes for 10 consecutive days.

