**Methods/Design::**

This study is a prospective, randomized, controlled, open trial. We randomly divided 42 subjects, aged 35 to 80 years, diagnosed with ischemic stroke within 1 month, into 2 groups with a ratio of 1:1. On the basis of this medical treatment, patients in the experimental group received 1 Hz rTMS in M1 area on the contralateral side, and 3 Hz rTMS treatment at Neiguan point and Sanyinjiao point on the affected side. The control group was treated with acupuncture (body acupuncture). All patients were treated once a day and followed up for 10 days. The National Institute of Health Stroke Scale score, simplified fulg Meyer, modified Barthel index, and cortical excitability were evaluated on the day of enrollment and the 10th day of treatment respectively. The modified Barthe index was followed up on the 30th day of treatment, and the adverse reactions were recorded at any time. The mechanism of rTMS will be revealed by Barthe index before treatment, on the 10th day of treatment and on the 30th day of follow-up. The results were analyzed by spss19.0 software, and the quantitative indexes were analyzed by *t* test and rank sum test. *χ*^2^ test was used for non-grade counting, and rank sum test was used for grade counting. All statistical tests were performed with bilateral test. If *P* value is less than or equal to .05, the difference will be considered statistically significant.

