### Study design

2.1

This study is a single-center, randomized, controlled, open clinical trial. A total of 42 participants will be randomly divided into 2 groups with a ratio of 1:1. Both groups were given basic treatment (cerebrovascular disease medical treatment, rehabilitation treatment). In addition to the basic treatment, the experimental group received 1 Hz rTMS in M1 area of the healthy side, and 3 Hz rMS treatment at PC6 and SP6 on the affected side. The control group was treated with acupuncture.

The whole study period was 30 days, including 10 days of treatment and 20 days of follow-up. Before treatment and on the 10th day of treatment and the 20th day of follow-up, the clinical efficacy evaluation scale was used to evaluate the subjects, and the cortical excitability was detected by rMS before and on the 10th day of treatment (Fig. 1).

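### The coil-placement step in section 2.7.1 (right dorsolateral prefrontal cortex, then 6 cm to the right) contradicts the stated central target, M1 of the healthy hemisphere

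*Protocol article*

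**What the plan says.** The central target is stated consistently outside the disputed clause. The abstract says that "patients in the experimental group received 1 Hz rTMS in M1 area on the contralateral side". Section 2.1 says that "the experimental group received 1 Hz rTMS in M1 area of the healthy side", and section 2.7 repeats M1 of the healthy side. Section 2.7.1 itself opens with M1: "rTMS stimulation of contralateral M1 area was applied to the rehabilitation of limb function after stroke". The figure 1 caption and the Discussion also name M1.

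Section 2.7.1 then sets out the procedure in three steps.

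- **Motor-threshold test.** "When stimulating M1 area, the coil should be tangent to the scalp", and "Adjust the coil to obtain the maximum amplitude and the best MEP repeatability". The resting motor threshold is then found from contractions of a thumb muscle.
- **Localisation of the treatment site.** The step begins "localizing the stimulation area: when stimulating the motor cortex of the thumb on the right dorsolateral prefrontal cortex (r-dlpfc) on the scalp" and continues "the stimulation coil was placed on the right dorsolateral prefrontal cortex (r-dlpfc) on the scalp, then 6 cm to the right". The PC6 and SP6 positions follow.
- **Stimulation parameters.** For the central site these are 1 Hz, 900 pulses and 90% of resting motor threshold.

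The schedule closes the section: "Participants will be treated once a day for 25 minutes for 10 consecutive days".

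**The concern.** The localisation step is the article's rule for where the treatment coil goes. For the acupoints it gives usable anatomical landmarks. For the cortex it names a prefrontal region on the right, with a further displacement to the right, where the design calls for the primary motor cortex of whichever hemisphere is unaffected.

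The trial is meant to test M1 stimulation combined with stimulation at two acupoints. If the printed step were followed, the central half of that combination would not be delivered as described, and a result in either direction could not be attributed to M1 stimulation. In patients with a right-hemisphere infarct the coil would also lie over the hemisphere that the design does not intend to stimulate. The Discussion offers the study as a basis for later multicenter research, and another site could not reproduce this step as printed.

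**Working it through.** No figure in the plan is in dispute, so the check is mainly a comparison of texts.

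**1. Region**

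| Place in the article | Cortical site |
|---|---|
| Abstract (Methods/Design) | M1, contralateral |
| 2.1 Study design | M1, healthy side |
| Figure 1 caption | M1 |
| 2.7 Interventions | M1, healthy side |
| 2.7.1, opening | M1, contralateral |
| 2.7.1, motor-threshold test | M1 |
| 2.7.1, localisation step | Right dorsolateral prefrontal cortex, then 6 cm to the right |
| Discussion | M1 |

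The dorsolateral prefrontal cortex appears in this one sentence and nowhere else in the article.

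**2. Side.** Section 2.3.1 requires unilateral limb paralysis from a basal ganglia or corona radiata infarct and does not restrict the side. The healthy hemisphere is therefore the right one for left-hemisphere infarcts and the left one for right-hemisphere infarcts. An instruction that always says right can match the design only for the first group. The article does not give the expected split by side, so no share of patients is estimated.

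**3. Can the clause be read as healthy-side M1?**

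- *Read literally:* the coil sits on the right prefrontal site, or 6 cm to the right of it. Neither is M1.
- *Read with the thumb motor area as a reference point only:* the coil still ends on, or is measured from, the right prefrontal site, and the side is still fixed.
- *Read with the motor-threshold test:* the MEP adjustment does find M1, but it belongs to the preceding step. Nothing says that this position is kept for treatment, and the next step gives another one.

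None of the three readings yields M1 of the unaffected hemisphere.

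**4. How much of the intervention the clause governs.** Inputs from sections 2.5 and 2.7.1: 21 experimental patients, 900 central pulses per session at 1 Hz, sessions of 25 minutes, 10 daily sessions.

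- Central pulses per patient: 900 × 10 = 9,000.
- Central stimulation time per session: 900 pulses ÷ 1 pulse per second = 900 s = 15 min.
- Share of the session: 15 ÷ 25 = 60%.

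These figures give the planned exposure that depends on the clause. They do not measure misplacement that has occurred. The PC6 and SP6 positions are unaffected.

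**The case against.** The strongest reply is that this is a wording fault and not a rival target. The clause itself speaks of stimulating the thumb area of the motor cortex, and it repeats the prefrontal phrase twice in one sentence, as a translation or pasting error would. Every other statement of the target agrees on M1. The same paragraph also contains a workable way to find M1, the MEP adjustment. The two treating physicians receive specific training (section 2.14), and operators must have more than three years of training in acupuncture and rTMS (section 2.7). A full protocol or operating procedure may give the placement correctly. On this view trained operators would ignore a clause that makes no anatomical sense, and another site could reconstruct the method from the rest of the article.

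Much of this stands. M1 was probably intended, harm depends on the clause having been followed, and the reproducibility complaint applies to the placement step and not to the whole intervention. The contradiction remains, however. The MEP sentence sits under the threshold test and does not override the localisation step that follows it. Nor is this a detail that an article has merely left out: it states a region, a side and a distance, and they conflict with the article's own target.

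**Conclusion.** The concern holds. The localisation step in section 2.7.1 contradicts the stated target in cortical region for every patient, and in side for any patient with a right-hemisphere infarct. It bears on the central component for the 21 experimental patients, 9,000 pulses each, but only on the assumption that the clause was followed, and the article does not show whether it was. The target itself is not in doubt; the placement instruction is wrong. Sample size and power are untouched, and no loss of effect is claimed. It should be corrected, because it is an operative rule for delivering the intervention under test.

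**What to change.** Delete the prefrontal and 6 cm wording in section 2.7.1 and replace it with: *The treatment coil is placed tangent to the scalp at the thumb-muscle MEP hotspot over M1 of the unaffected hemisphere, left or right according to lesion side.* This uses the MEP procedure that the section already describes.

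The investigators should confirm that this is the intended site and state which site was used for any patient already treated; section 2.6 opens the study period on August 1, 2019.

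If the printed clause was only a reporting error, the cost is a text correction and a note to the two treating physicians. If it has governed delivery, the change alters how the study is carried out and must go back to the ethics committee under section 2.2, and the site used should be checked for the patients concerned. The record card in section 2.14 is described as holding the treatment date, personal information and a signature, with no mention of coil site, so that check may have to rest on the operators' account. The correction itself needs no new visit, procedure or data item.

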**Figure 2 F2:**
[figure not shown]
Location of Neiguan (PC 6) Acupoint. Longxiang H. WHO Standard Acupuncture Point Locations in the Western Pacific Region (Chinese-English bilingual edition) [M]. Beijing: People's Medical Publishing House, 2010.

**Figure 3 F3:**
[figure not shown]
Location of Sanyinjiao (SP 6) Acupoint. Longxiang H. WHO Standard Acupuncture Point Locations in the Western Pacific Region (Chinese-English bilingual edition) [M]. Beijing: People's Medical Publishing House, 2010.

#### Positive-control group

2.7.2

In addition to the basic treatment, the patients in the control group also need to be given corresponding acupuncture treatment. According to the theory of traditional Chinese medicine, acupuncture position and parameters were selected^[19,20]^: upper limbs (bilateral): Hegu, Neiguan, Shousanli, Quchi, Jianli; lower limbs (bilateral): Taichong, Xuanzhong, Sanyinjiao, Zusanli, Yanglingquan, Fengshi; head: Baihui, Fengchi (bilateral). Patients will be treated once a day for 10 consecutive days.

### Adverse events observation

2.8

#### Adverse reactions and countermeasures of magnetic stimulation

2.8.1

Magnetic stimulation may induce epilepsy, local skin numbness, pain and discomfort, and other adverse reactions. In the treatment process, the intensity, frequency, and stimulation times can be changed according to the patient's condition to reduce the occurrence of adverse reactions.^[21–23]^ During the study, a patient treatment log will be established to monitor all adverse reactions during treatment and follow-up, and appropriate intervention will be carried out. If serious adverse reactions occur during the treatment, they should be reported to the principal investigator immediately, and the details should be recorded in the patient's treatment log and corresponding treatment measures should be taken, such as adjusting the coil position and stimulation intensity to avoid stimulating the sensitive orbitofrontal cortex (100% RMT → 80% RMT), or giving appropriate medical intervention according to the patient's condition. If the subject or researcher thinks that the patient cannot tolerate these adverse reactions, the trial can be terminated and the subject will withdraw from the study.

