#### Adverse reactions of acupuncture and countermeasures

2.8.2

Acupuncture may cause acupuncture syncope, convulsion, severe pain, stuck needle, broken needle, local infection and subcutaneous hematoma and other adverse reactions. However, they are generally mild reactions, and the prognosis is generally good after corresponding treatment.^[24]^ According to the causes of adverse reactions and the degree of adverse reactions, symptomatic treatment can be carried out, such as: detailed medical history to avoid convulsion, appropriate psychological counseling to avoid fainting, standardized needle application, auxiliary manipulation to avoid needle sticking, pain, broken needle, etc. If there are serious adverse reactions, they should be reported to the principal investigator immediately, and the details of adverse reactions should be recorded in the patient's log, and medical intervention should be carried out. If the subject or researcher thinks that the patient cannot tolerate these adverse reactions, the trial can be terminated and the subject will withdraw from the study.

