### Statistical analysis

2.13

According to the situation of data collection, data analysis will be based on the principle of intention to treat analysis (ITT) and/or per protocol analysis (PP). We will also evaluate the group effect by comparing the analysis results of the above 2 data sets to evaluate the accuracy of our analysis results.

All data will be analyzed by third-party statisticians using spss23.0 (v23.0, SPSS Inc, Chicago, IL). *P* < .05 was significant. Descriptive statistics will be carried out by group and time for average, standard deviation, maximum value, minimum value, and so on.

The data of the patients were collected and summarized. The quantitative indexes were *t* test and rank sum test. *χ*^2^ test (ANOVA) was used for non-rank counting, and rank sum test was used for grade counting. All statistical tests were performed with bilateral test. If *P* value is less than or equal to .05, the difference will be considered statistically significant.

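### The exit rules in 2.8.1, 2.8.2 and 2.3.3 do not separate stopping treatment from leaving the study, so outcome-related loss can weaken the ITT option

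*Protocol article*

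**What the plan says.** Section 2.8.1 covers reactions to magnetic stimulation. For serious reactions it offers measures short of exit, such as "adjusting the coil position and stimulation intensity" or medical care. Then, if the subject or researcher thinks "the patient cannot tolerate these adverse reactions, the trial can be terminated and the subject will withdraw from the study", participation ends. Section 2.8.2 closes the acupuncture paragraph with the same consequence: "the trial can be terminated and the subject will withdraw from the study".

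Section 2.3.3 is a single list of seven withdrawal criteria. Item 2 is "Those who fail to treat according to the regulations affect the evaluation of curative effect". Items 4 and 5 stand side by side as "4.Loss to follow-up.5.Serious adverse events". Item 7 is "New infarct or secondary hemorrhage occurred and the condition deteriorated". Item 3 is withdrawn consent.

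Section 2.13 states that "data analysis will be based on the principle of intention to treat analysis (ITT) and/or per protocol analysis (PP", and that results from the two sets will be compared. Section 2.8.1 also promises a treatment log to "monitor all adverse reactions during treatment and follow-up". Sections 2.10 and 2.14 provide for recording withdrawals and their reasons. Section 2.12 describes an open trial with third-party evaluation.

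**The concern.** An ITT analysis needs outcomes from randomised patients whether or not they completed treatment. The article's wording ties the end of treatment to the end of participation. For intolerable reactions it does so explicitly; for items 2, 5 and 7 it does so by placing them in the same list as true study exits.

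Some of these triggers are related to the outcome. Item 7 requires that the patient has worsened, and NIHSS, FMA and MBI are the primary outcomes. In an open trial, where patient or researcher judges tolerability and the two treatments have different expected reactions, the loss may also differ between arms. Patients can be kept in the ITT set by definition, but no analysis recovers a score that was never taken. Safety is affected too: a patient who exits because of an event may drop out of adverse-event observation at the moment it matters most.

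**Working it through.** **1. What an exit removes.** Section 2.9 schedules NIHSS and FMA before treatment and at day 10, and MBI also at the last visit, taken here as day 30 of the 30-day study in 2.1.

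| Time of exit | Primary-outcome data at risk |
|---|---|
| Before day 10 | Day-10 NIHSS, FMA and MBI; day-30 MBI |
| Day 10 to day 30 | Day-30 MBI |

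On the 2.9 schedule, NIHSS and FMA have only one post-baseline assessment, so exit before day 10 leaves no post-baseline value for either. Adverse-event observation after exit is at risk in both rows.

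**2. How clear each exit rule is.**

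| Trigger | Does the text say the patient leaves the study? | Link to outcome |
|---|---|---|
| Intolerable reaction (2.8.1, 2.8.2) | Yes | Possible, not shown |
| Item 2, non-adherence affecting the efficacy evaluation | Not spelled out | Possible |
| Item 5, serious adverse event | Not spelled out | Plausible |
| Item 7, new infarct or haemorrhage with worsening | Not spelled out | Direct |

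No section keeps the day-10 or day-30 assessments for any of these patients.

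**3. The plan's own loss allowance (2.11).** Taking its inputs as given:

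- n per arm = 2 × 1.93² × 10.5 / (8.95 − 6.90)² = 78.22 / 4.2025 = 18.61, rounded up to 19. This matches the plan.
- Total = 19 × 2 × 1.10 = 41.8, rounded to 42. This matches the plan.
- Allowance = 42 − 38 = 4 patients.

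**4. Share of an arm lost (21 per arm).**

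- One patient: 1/21 = 4.8%.
- Four patients split 2 and 2: 2/21 = 9.5% in each arm.
- Four patients in one arm: 4/21 = 19.0% against 0/21 = 0%.

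That the whole allowance is used, and how it splits, are assumptions.

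**5. Illustration of the mechanism, not an estimate.** Assume no true difference, normal scores with SD 1.93, 21 per arm, a two-sided t test at 5%, and that the k worst NIHSS values are missing from one arm only (100,000 simulated trials).

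| k lost | Shift in mean difference (NIHSS points) | Two-sided error |
|---|---|---|
| 0 | 0.00 | 5.1% |
| 1 | 0.18 | 6.8% |
| 2 | 0.33 | 9.8% |
| 3 | 0.48 | 14.2% |
| 4 | 0.62 | 19.6% |

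This is a deliberate extreme. Loss that is balanced between arms, or less tied to outcome, biases less. It shows that a few patients can matter at this sample size, and that the 10% allowance protects patient numbers (power 0.906 with 19 per arm on the plan's inputs), not the validity of the comparison.

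**The case against.** The strongest reply is that much of this rests on silence. Only 2.8 says outright that the patient leaves the study; items 2, 5 and 7 are entries under a heading, and a condensed article may leave follow-up after treatment stops to the full protocol. This stands in part: the 2.3.3 limb concerns wording that fails to separate two things, not an explicit order to stop assessing. The 2.8 sentence, however, is a rule stated for both arms, and a fuller document would have to override it.

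It is also fair that 2.8 is narrow. Exit needs a judgement of intolerability, 2.8.1 offers adjustment or care first, 2.8.2 describes acupuncture reactions as generally mild, and nothing shows that intolerance tracks NIHSS, FMA or MBI. Item 2 likewise covers only non-adherence that affects the efficacy evaluation. The outcome-related argument is therefore clearest for item 7.

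The plan has mitigations: third-party evaluation, the comparison of ITT and PP results, and recorded reasons for withdrawal. None supplies a score for a patient who was not assessed.

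A reader might infer that the plan contradicts ITT, or that it orders these patients out of the analysis. The documents do not support either: 2.13 keeps the ITT option open, and no section excludes withdrawn patients from the ITT set. Nor can the simulated error rates be read as the trial's expected error; they come from an assumed one-sided loss of the worst patients.

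**Conclusion.** The point holds as a weakness in the stated exit rules. Intolerable reactions lead explicitly to study exit, and 2.3.3 mixes reasons to stop treatment with reasons to leave the study. Followed as written, this can lose primary-outcome and safety data for patients whose exit is partly related to outcome, most clearly under item 7, and so weakens the ITT option.

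The size of any bias cannot be estimated: the article gives no withdrawal rate by cause and no outcomes for withdrawn patients. Only the counting is firm: 4.8% of an arm per patient and an allowance of 4 patients. The conclusion assumes that the article's wording is what sites follow; a full protocol that keeps assessing these patients would remove the problem. This is a cheap improvement worth making, not a defect that invalidates the design.

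**What to change.** **Sections 2.8.1 and 2.8.2.** Replace "the trial can be terminated and the subject will withdraw from the study" with: *study treatment stops; unless the patient withdraws consent to follow-up, the patient stays in the study and is assessed at day 10 and day 30.*

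**Section 2.3.3.** Move items 2, 5 and 7 to a separate list of treatment-discontinuation criteria:

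- Item 7: treatment must stop.
- Item 5: treatment must stop where the adjustment or medical care described in 2.8 is not enough.
- Item 2: non-adherence is recorded and affects only the PP set.

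Among these grounds, keep study withdrawal only for withdrawn consent (item 3) and loss to follow-up (item 4). Collect adverse events and the existing day-10 and day-30 assessments, where feasible, for every randomised patient.

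**Cost.** A wording change in three sections and a few extra follow-up contacts for patients who stopped treatment. The visits already exist within the 30-day study, the sample size does not change, and patients can still stop a treatment they cannot tolerate.
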